#### Theoretical backdrop: multi-process action control model

To enhance the effectiveness and implementation of the intervention, the Multi-Process Action Control model (M-PAC) will be used as the theoretical backdrop [63]. The M-PAC model postulates that individuals’ behavioral change is a continued process from intention formation to behavioral initiation and maintenance, consisting of reflective, regulatory, and reflexive processes [64]. In the M-PAC framework, intention is conceived as a decisional construct (i.e., has intention/ has no intention). Similar with the tenets of other psychosocial theories (e.g., the Theory of Planned Behavior, TBP; Capability, Opportunity, Motivation, Behavior model, COM-B), the M-PAC emphasizes the influence of several determinants of intention which function in the reflective processes (i.e., consciously deliberated and expected consequences of performing a behavior) [65]. Particularly, instrumental attitude (e.g., PA is useful), affective attitude (e.g., PA is enjoyable), perceived capability (e.g., I have the ability to perform a behavior), and perceived opportunity (e.g., I have the time and can access to perform PA) play a crucial role in forming a behavioral intention [66]. Furthermore, the M-PAC framework proposes that whether a behavioral intention can be successfully translated to an actual behavior is determined by the reflective processes of affective attitude and perceived opportunity as well as the enactment of regulation processes. Particularly, higher levels of affective attitude and perceived opportunity are considered necessary for successful translation of behavioral intention into actual behavior than for intention formation. Similar with the Health Action Process Approach (HAPA), the M-PAC framework also suggests the importance of regulatory strategies (e.g., action planning and coping planning) in the intention-behavior translation [67]. In addition, extending on previous psychosocial theories, the M-PAC framework highlights the important role of diverse impulsive components in behavioral maintenance (i.e., “continuance of actional control is thought to rely upon the development of reflexive processes”) [68]. It suggests that impulsive components affect actional control most often through learned associations and are triggered through specific circumstances/cues and stimuli [69]. The M-PAC framework emphasizes the development of two crucial reflexive processes, including habit (e.g., I will engage in PA automatically) and identity (e.g., I am a person who is physically active), as individuals begin to perform the behavior more regularly [63–65]. Therefore, a developed behavioral pattern of action control will be determined by the independent influence of relative, regulatory, and reflexive processes [63–65]. Targeting the psychosocial components of the M-PAC model, a series of Behavioral Change Techniques (BCTs) will be also adopted [70, 71] in the FMSPPOC program (see Table 1).

**Table 1 Tab1:** M-PAC components and behavioral change techniques involved in the FMSPPOC

Approach	Time	Target objects	M-PAC components	Behavioral change techniques (BCT) addressed	Examples
Briefing sessions & Education materials	Week 1, 2, 12 & 13	Parents and children	Perceived capability; Instrumental attitude; Perceived opportunity; Affective attitude	- Instruction on how to perform a behavior (4.1) - Information about health consequences (5.1) - Information about social and environmental consequences (5.3 & 5.6) - Information on others’ approval (6.3) - Restructuring the physical environment (12.1) - Prompts/cues (7.1) - Feedback on behavior (2.2)	Introducing the benefits of participating in PA regularly, and the negative consequences of physical inactive; Introducing the importance of FMSs, especially for obese children; Introducing the feasible and pragmatic approaches (e.g., PA) to develop FMSs; Introducing the nature and content of the FMSPPOC program
School-based PA sessions delivered by PE teachers	Week 1–12	Children	Perceived capability; Instrumental attitude; Perceived opportunity; Affective attitude	- Instruction on how to perform a behavior (4.1) - Behavioral practice (8.1) - Feedback on behavior (2.2) - Verbal persuasion (15.1) - Social comparison (6.2) - Prompts/cues (7.1)	PE teachers will teach participants how to play the ball games, guide them to practice, and provide them with immediate feedback; Participants will learn and practice the PA sessions; Group activities will be implemented during the PA sessions; PE teachers and peers will provide verbal encouragement; A weekly peer role model will be selected by participants and teachers
Family-based PA assignments completed by both parents and children	Week 1–12	Parents, children, and other social networks	Perceived opportunity; Affective attitude; Behavioral regulation	- Restructuring the physical environment (12.1) - Prompts/cues (7.1) - Behavioral practice (8.1) - Feedback on behavior (2.2) - Practical support (3.2) - Emotional support (3.3) - Problem solving (1.2) - Action planning (1.4) - Goal setting (behavior) (1.1) - Self-monitoring of behavior (2.3)	Parents will be taught how to establish a favorable PA environment at home; Parent–child co-activity will be implemented; Parents will be asked to provide their child/children with verbal encouragement; A short-term goal and a long-term goal will be set; Incentive will be provided based on the engagement of family-based PA assignment; Ranking games will be implemented; Parents will be asked to monitor the child/children’s PA performance and upload on the website
Online and offline workshops	Week 14, 16, 18, 20, 22 & 24	Parents and children	Perceived capability; Instrumental attitude; Perceived opportunity; Affective attitude; Behavioral regulation; Identity; Habit	- Information about health consequences (5.1) - Information about social and environmental consequences (5.3 & 5.6) - Information on others’ approval - Behavioral practice (8.1) - Feedback on behavior (2.2) - Problem solving (1.2) - Review about goals (1.5) - Self-monitoring of behavior (2.3) - Behavioral substitution (8.2) - Habit formation (8.3) - Unspecified support (3.1) - Practical support (3.2) - Emotional support (3.3) - Prompts/cues (7.1)	Relevant knowledge such as long-term development of FMSs, benefits and consequences of healthy lifestyles, and potential risks of FMSs development will be delivered; Acute PA practice will be implemented; Problems will be discussed during the workshops and solutions will be confirmed by experts, PE teachers, parents and child/children on consensus; Feedback on behaviors and goals will be provided by PE teachers, experts and parents; Values and meaning of the activity as well as other tactics (e.g., visual and tactile symbols) of the new identity will be emphasized

#### 12-week initiation phase

During the first 12-week initiation phase, the intervention consists of school-based PA sessions and family-based PA assignments for the whole classes including the obese children to prevent stigmatization or exclusion. Particularly, the school-based PA sessions will be delivered twice a week (90 min each session) for 12 weeks (totally 24 sessions). Three ball games (i.e., soccer, basketball, and volleyball) will be used as the main content of school-based PA sessions for FMSs promotion due to the consideration of effectiveness, enjoyment, feasibility, and greater adherence [72, 73]. Each session will include a 5-min warm-up, a 15-min physical fitness training, a 60-min FMSs training (30-min learning and practice + 30-min game), and a 10-min cool-down. For the FMSs training part, three types of ball games will be delivered in different weeks, including week 1–4 for soccer, week 5–8 for basketball, and week 9–12 for volleyball. Each ball game section will include skill instruction and learning, skill practice (guided by teachers + self), game part, and review/summary. All the movements in each section will be designed to achieve a moderate-to-vigorous intensity. Detailed content of the school-based PA sessions can be found in Table 2.

**Table 2 Tab2:** The content of the school-based PA sessions

PA-sessions (Time allocation)	Warm-up (5-min)	Physical fitness training (15-min)	FMSs training (60-min)		Cool-down (10-min)
			30-min learning & practice	30-min game	
**Week 1–4:** Soccer FMSs training	50–60% HR_max_ Jogging, dynamic stretching of limbs and trunk muscles The PE teacher will briefly introduce the course content and objectives during the warm-up	70–90%HR_max_ 2–3 sets of combined exercise: 1) 5 × 10 shuttle run; 2) 50 m sprint 3) 10–15 push-ups 4) 20–30 deep squats; 5) 20–30 sit-ups; 6) 30-60 s basic hip bridge; 7) 30-60 s plank; 8) 30-60 s jumping jacks; 9) 30-60 s high knees The PE teacher will select 6–8 movements to practice; During the interval, 1-min mark time will be performed during the recovery interval	70–90%HR_max_ Practice in small groups: 1) Off-ball; 2) Throw-Ins; 3) Simple dribbling, passing and shooting; 4) Trapping; 5) Juggling	70–90%HR_max_ Group-based game: 1) Dribble game; 2) Juggling soccer game; 3) Spot shooting game; 4) Small-size soccer match: 3 vs 3 or 5 vs 5	50–60% HR_max_ Dynamic stretching and relaxation of the limbs and trunk muscles Teachers will introduce common knowledge or stories related to soccer, basketball, and volleyball according to the progress of the PA sessions Participants will be asked to share their feelings about the PA sessions
**Week 5–8:** Basketball FMSs training			70–90%HR_max_ Practice in small groups: 1) Passing (e.g., chest, push and bounce) and catching; 2) Dribbling (single or both hands); 3) Shooting (spot or move); 4) Foot work; 5) Layups (both hands)	70–90%HR_max_ Group-based game: 1) Fixed-point shots; 2) Passing and catching games; 3) Dribbling relays; 4) Small-size basketball match: 3 vs 3 or 5 vs 5	
**Week 9–12:** Volleyball FMS training			70–90%HR_max_ Practice in small groups: 1) Multi-directional forms of running, jumping, and skipping; 2) Passing (e.g., proper hand placement, proper stance, dig pass); 3) Serving (e.g., practice serving the ball against the wall or partner); 4) Setting (e.g., pass the ball to a teammate or over the net to the opposing team); 5) Triangle passing drill	70–90%HR_max_ Group-based game: 1) Dig pass game; 2) Dig pass over the net game; 3) Serve and run drill game 4) Butterfly passing drill game	

In addition to school-based PA training, all the participants are asked to complete a 30-min family-based PA assignment at least three times per week during the first 12-week initiation phase. The purpose of the family-based PA assignment is to reinforce FMSs practice and promote PA engagement during the out-of-school time. For each PA assignment, participants are asked to complete several activities together with their parents (i.e., parent–child co-activity). These activities are modified from the school-based PA sessions that can be easily undertaken in a family-setting (e.g., require minimal equipment, can be undertaken indoors or outdoors within limited space). Parents will also be asked to track their child/children’s weekly completion times and conditions and upload this information to a designated column of the Ding-Talk APP (https://www.dingtalk.com/en, Alibaba Group). At weekends, the research team members will check the participants’ PA assignments and reward them with small red flower stickers as incentives: participants who complete PA assignments three times will receive one sticker while who complete the assignments five times or more will receive two stickers. The greater number of red flowers participants accumulates, the more prizes (e.g., sports bracelets, suits, and sneakers) they can redeem at the end of the intervention.

#### 12-week maintenance phase

12-week maintenance phase will be implemented mainly during the summer holidays following the 12-week initial phase. This part will consist of three face-to-face workshops with three online webinars (using Ding-Talk APP) only for the target population of obese children. The offline workshops and online webinars will be conducted alternatively and biweekly. Each workshop and webinar will last for 60 min, consisting of 30-min expert talk, 20-min interactive activity, and 10-min Q&A. The main purposes of the offline workshops and online webinars will include: (1) maintaining children’s FMSs practice; (2) promoting healthy lifestyles (e.g., regular engagement of PA, limited sedentary time, high quality sleep, balanced diet) in the long run; (3) addressing existing problems and future challenges. The topics will include (1) practicing FMSs in daily life (e.g., FMSs games introduction, tips of FMSs practice); (2) PA and health (e.g., recommendation of PA for children, co-activities of parent and child); (3) sedentary behavior and health (e.g., recommendation of screen time, tips of interrupting prolonged sitting); (4) good sleep (e.g., sleep recommendation in terms of the duration and quality); (5) eating happily and healthily (e.g., healthy food selection, healthy cooking, and “say no to snacks”); (6) existing problems and future challenges in children’s FMSs (e.g., existing problems in daily practice of FMSs, how to maintain the development of FMSs after the project completion).

### Procedure and quality control

The FMSPPOC development will be facilitated through five steps. Step 1 is to form a steering group, consisting of relevant stakeholders (e.g., research team members, PA instructors, primary school managers, and obese children and their parents). In Step 2, the research group will develop the intervention content and practical strategies. In the 3rd step of program production, all the stakeholders will discuss on consensus with respect to the refining and confirming of the intervention content and practical strategies, and then a two-month pilot study will be conducted to test and optimize the strategies and relevant materials. Participant recruitment and maintenance, data collection instrument and schedule, adaptability and feasibility of the intervention will be fully considered in the pilot study. In Step 4, a comprehensive plan for the intervention implementation will be constructed. To ensure the safety, supportiveness, enjoyment, and efficiency of the intervention during the implementation. An operational manual and training materials will be developed in this step. In Step 5, a plan to evaluate the implementation and effectiveness of the intervention will be developed. Any amendments will be made if necessary (Fig. 2).

**Fig. 2 Fig2:**
[figure not shown]
Gantt chart of research activities

For the project implementation, two 60-min face-to-face briefing sessions will be first provided for the intervention facilitators (i.e., PE teachers, student helpers, parents) one month prior to the FMSPPOC commencement (delivered by the investigators and/or research assistant) in the university gymnasium. One briefing session will focus on necessary knowledge and skills training so that PE teachers and student helpers can implement the intervention plan smoothly and effectively. In addition, the implementation details, rationale, nature, and benefits of FMSPPOC will be introduced. Another briefing session will train all evaluators on the measurement of FMSs, health behaviors, and physical fitness, as well as the specification of psychological measures.

For the main study, the school-based PA sessions will be conducted in an indoor playground at a primary school during afternoon custody time (4:00–5:00 p.m.) by qualified PE teachers with assistance of student helpers. The attendance of participants will be also recorded. In addition, to monitor the PA intensity, three mid-tests will be conducted using downloadable, wireless Polar Team Pro (Polar Team Pro, Kempele, Finland) and Polar heart rate sensor during the ball games (week 3, 7, & 11).

For the family-based PA assignments, relevant tasks and instructions will be introduced for parents in the beginning briefing session. The research assistants will remind parents to upload the required information each week via SMS messages and deliver the incentives correspondingly. For the second 12-week maintenance phase, the offline workshops will be implemented at a multi-function sports room in a primary school, while the online webinars will be conducted using Ding-Talk APP. These workshops and webinars will be facilitated by trained PE teachers and health experts from Hebei Normal University. Each participant will be asked to attend the workshops and webinars with at least one parent or legal guardian.

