## Method

### Study design

This study will apply a two-group double-blinded cluster randomized controlled trial (CRCT) with four measurement occasions, including baseline assessment (T0), mid-intervention assessment (T1: 12 weeks after the baseline assessment), post-intervention assessment (T2: 24 weeks after the baseline assessment), and follow-up assessment (T3: 48 weeks after the baseline assessment). Two groups include: 1) an intervention group (IG), receiving the FMSPPOC intervention for 24 weeks; and 2) a waiting-list control group (WCG), receiving the FMSPPOC intervention or relevant materials (based on participants’ requirements) after the completion of all data collection for IG (see Fig. 1). The design, implementation, and reporting of the FMSPPOC will follow the SPIRIT guidelines and the CONSORT statement [54, 55] (Supplement Material 1). The study protocol was approved by the Research Ethics Committee of Hebei Normal University (ref. No.2021LLSC051). This study was a key part of a large research project funded by the National Social Sciences Funding Committee of China (Ref. No.: 19200526).

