#### Randomization and blinding

To avoid the potential for contamination, randomization will be conducted at the school level. All eligible schools will be randomly assigned to one of the two groups prior to baseline assessment, where each group will consist of three schools. Each school will select 28 obese children from four classes covering grades 2–5 to participate in this study, and the children in the same school will receive the same treatment. Randomization will be implemented with a ratio of 1:1, using the Excel software by a researcher who will not be involved in the participant recruitment, data collection or evaluation. Due the ethical concerns, participants are not able to be blinded as they will be informed with the study purpose and group allocation in the written informed consent form. Intervention facilitators and outcome evaluators will be concealed for the group allocation.

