Perceived motor competence	Assessed using the subscale (athletic competence) of the Self-perception Profile for Children (SPPC) [85]. Athletic competence subscale of SPPC includes 6 items, three of the items are worded such that the first part of the statement reflects low competence or adequacy, and three are worded to first reflect high perceptions of competence or adequacy. This counterbalancing is reflected in the scoring of items, where half of the items are scored 1, 2, 3, 4 and half are scored 4, 3, 2, 1. This is to insure that children are tracking the content of the items and are not simply providing random response choices or are always checking the same side of all questions. In addition, the Chinese version of the SPPC has adequate reliability, ranging from 0.61 to 0.76 [86]. The structure and criterion validity are acceptable [87]
Perceived well-being	The Chinese version of the 12-item Psychological Well-Being Scale for Children (PWB-C) will be used [88, 89]. PWB-C contains six dimensions of psychological well-being: environmental mastery, personal growth, purpose in life, self-acceptance, autonomy, and positive relations with others. Options were given on a 4-point Likert scale, ranging from 1 (“almost never”) to 4 (“very frequently”). The mean score of the 12 items will be calculated, with a higher score indicating a higher level of perceived well-being
M-PAC components of PA for both parents and children	The Chinese translated items of M-PAC components of PA will be used [90–92]. The questionnaire package includes measures for behavioral intention, instrumental and affective attitudes, perceived capability, perceived opportunity, parental support (intentional and actual), action planning and coping planning, action control, habit strength, and identity. The response options and scoring approach will be consistent with the settings in previous studies [65, 66, 90, 91]

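### The first parent briefing has two dates, and the earlier one, a month before programme start, falls before baseline and probably in intervention schools only

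*Protocol article*

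**What the plan says.** All references are to the protocol article.

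- **Pre-start briefing (Procedure and quality control, text after Fig. 2).** Two 60-minute sessions are "provided for the intervention facilitators (i.e., PE teachers, student helpers, parents) one month prior to the FMSPPOC commencement". On the first: "One briefing session will focus on necessary knowledge and skills training so that PE teachers and student helpers can implement the intervention plan". The next sentence adds that "the implementation details, rationale, nature, and benefits of FMSPPOC will be introduced", without naming an audience. On the second: "Another briefing session will train all evaluators on the measurement of FMSs, health behaviors, and physical fitness".
- **Parents' tasks (same section).** For the home assignments, "relevant tasks and instructions will be introduced for parents in the beginning briefing session". That session is not dated.
- **Table 1.** Briefing sessions and education materials are an active component aimed at parents and children. They target perceived capability, perceived opportunity, and instrumental and affective attitude, and they are placed in weeks 1, 2, 12 and 13.
- **Visits (Study design).** "mid-intervention assessment (T1: 12 weeks after the baseline assessment"; T2 is the post-intervention visit, 24 weeks from baseline. The programme is 12 + 12 weeks, and Table 1 has the last workshop in week 24.
- **Allocation (Randomization and blinding).** "All eligible schools will be randomly assigned to one of the two groups prior to baseline assessment". The same section says that facilitators and evaluators are kept unaware of allocation.
- **Outcomes and model.** Table 4 includes "M-PAC components of PA for both parents and children", parental support among them. Data analysis specifies mixed models adjusted for baseline values.

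**The concern.** Table 1 treats a briefing as part of the intervention: it carries coded behaviour-change techniques and aims at named psychosocial constructs. The pre-start sessions cover much the same ground (what the programme is, why it exists, what good it does). If parents hear this before T0, and only in schools already allocated to the programme, T0 is no longer a pre-intervention measurement for the outcomes that such a talk is meant to move.

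Three uses of T0 would suffer for those outcomes:

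- Baseline adjustment would remove part of the intervention effect.
- The baseline comparison of arms would mix chance imbalance with early exposure.
- A mediation model that uses change in M-PAC constructs from T0 would start from a shifted point.

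**Working it through.** **Inputs.** T1 and T2 lie 12 and 24 weeks from baseline (Study design). The programme lasts 24 weeks, with its last contact in week 24 (Table 1). An assessment round takes 10 days, with accelerometry on days 1–7 and psychological measures on day 10 (text after Table 4). The briefing is one month before the start, taken here as 30 days.

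**The plan's own timeline.** Let x be the weeks from the start of T0 to programme start. In programme time, T1 falls at 12 − x weeks and T2 at 24 − x weeks. The briefing precedes the start of T0 by 30 − 7x days.

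| Case | x (weeks) | T1 | T2 | Briefing ahead of T0 (days) |
|---|---|---|---|---|
| T0 starts with the programme | 0 | 12.0 | 24.0 | 30 |
| T0 round ends just before the start | 10/7 = 1.4 | 10.6 | 22.6 | 20 |
| T0 starts on the briefing day | 30/7 = 4.3 | 7.7 | 19.7 | 0 |
| T0 round ends before the briefing | 40/7 = 5.7 | 6.3 | 18.3 | −10 |

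The first row reproduces the stated schedule exactly. The second does too if the 12 and 24 weeks are counted from the end of the T0 round. In both rows the briefing comes first, by 20 to 30 days. A 28-day month would make this 18 to 28.

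**The reverse order.** Completing T0 before the briefing puts T2 at 18.3 weeks, or at 24 − 4.3 = 19.7 weeks if counted from the end of the round. Either way T2 precedes the week 22 and 24 workshops and is not post-intervention. T1, at 6.3 to 7.7 weeks, precedes the whole week 9–12 volleyball block.

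**How loose are the visit labels?** T3 is given as 48 weeks from baseline in Study design and as six months after the programme in Outcome evaluation, which is about 24 + 26 = 50 weeks. That is about 2 weeks of slack. Reversing the order needs 4.3 to 5.7 weeks.

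**Whether parents attend.** The bracketed list of facilitators includes parents. The two sessions as described name teachers and helpers in one and evaluators in the other. Table 1 starts parent briefings in week 1. These statements cannot all describe one schedule.

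**Direction of bias.** If an early briefing shifts T0 in the intervention arm by s, and the model's baseline slope is b, the adjusted effect falls by b × s. Only part is lost when b is below 1. The documents give neither b nor s. As pure assumption, b = 0.5 with s = 0.1 to 0.3 SD gives 0.05 to 0.15 SD; no outcome in the plan supports those inputs.

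**The case against.** The strongest reply is that exposure of parents before T0 is not shown. Neither pre-start session is described as a parent session, and the undated session that introduces parents' tasks fits Table 1's week 1. No place describes a briefing of children before week 1. This stands as a reason not to say that parents will be exposed. It does not remove the conflict, because the sentence that sets the date lists parents among those briefed.

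Other points on that side:

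- **Attendance by arm.** No text says which schools attend. Control schools receive the programme only after the intervention group's data collection, so only intervention schools need facilitators at this stage. One-arm attendance is therefore a strong inference, but it is not stated. The claim that facilitators are unaware of allocation sits badly with it and needs reconciling too.
- **Date of T0.** T0 is not dated against programme start, and the Gantt chart is not shown. The arithmetic still leaves little room for another order.
- **Primary outcome.** A reader might infer that T0 is compromised for every outcome. The documents do not support that. TGMD-3 and MABC-2 are performance tests, school sessions and home assignments begin in week 1, and nothing says teachers use the material earlier.
- **Consent.** Families learn the study purpose and their allocation from the consent form, so attitudes at T0 may be influenced even without a briefing. Moving the briefing removes one source and leaves the other.
- **Direction.** If the briefing moves scores favourably, the bias is towards no effect and would not create a false positive.

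**Conclusion.** The point holds in a limited form. The article contradicts itself on when parents are first briefed. Followed as written, the pre-start sentence puts a briefing about 20 to 30 days before T0 and after allocation. This rests on a month of about 30 days and on the T1 and T2 labels meaning what they say. That only intervention schools attend is probable but not stated.

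The outcomes plausibly at risk are M-PAC scores in parents and children and possibly accelerometer-measured activity. With baseline adjustment, effects on these would be partly understated and mediation results blurred. The documents do not allow the amount to be estimated, and the 0.05 to 0.15 SD illustration should not be read as a finding. The motor-skill primary outcome is not plausibly affected. This is a cheap improvement that protects secondary outcomes and does not threaten the main comparison.

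**What to change.** 1. Reconcile the pre-start briefing text with Table 1, and state who attends each session, from which schools, and when.
2. Complete T0 in all six schools before any briefing of intervention-arm parents or children on the programme, with Table 1's week 1 session as first parent contact. The whole 10-day round must close first: if T0 began on the first day of week 1, a week 1 briefing would precede the day 10 psychological measures.
3. State that no programme material is used with children before T0.
4. Reconcile the statement that facilitators are unaware of allocation with briefing them by school.

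Evaluator training should stay before T0. Training of PE teachers and student helpers can also stay there: the text after Table 4 has student helpers, assisted by PE teachers, collecting the day 8–10 data at every visit, so postponing all their training would leave T0 assessors untrained.

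The cost is a parent briefing about a month later than the pre-start text implies, plus a few sentences. No sessions or staff are added.
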